##### Data analysis and sample size

Mean levels of salt and sugar, overall and by product category, and individual product prices and mean prices for each product category for year 1, 3 and 5 will be calculated. Based on the 2013 processed food composition database, it is expected that data on around 1200 products will be collected each year. We will estimate the paired change in salt and sugar levels between baseline data and each of the follow-up points. Even if the percentage change in composition is highly dispersed (e.g. SD = 20) we should have 0.9 power to detect a 1% change in composition across all categories, or a 10% change for food categories with 50 items. We will analyse the change over time using linear mixed models which account for the repeated measurements.

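### Food-composition survey: 1200 products with SD 20 give about 0.41 power for a 1% change, not 0.9; the change detectable at 0.9 power is about 1.9%

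*Protocol article*

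**What the plan says.** The section Data analysis and sample size, under Assessing food composition and price of processed foods, gives everything needed to check its power claim except the significance level.

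- Number of products: "it is expected that data on around 1200 products will be collected each year".
- Comparison: "We will estimate the paired change in salt and sugar levels between baseline data and each of the follow-up points".
- Dispersion: "Even if the percentage change in composition is highly dispersed (e.g. SD = 20". This is the SD of the percentage change itself.
- Power: "we should have 0.9 power to detect a 1% change in composition across all categories, or a 10% change for food categories with 50 items".
- Model: "We will analyse the change over time using linear mixed models which account for the repeated measurements".

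The opening part of Methods lists salt and sugar levels in foods among the main outcome measures.

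**The concern.** The two halves of the power sentence share one SD and one power, so the detectable change should scale with 1/√n. Going from 50 to 1200 items multiplies n by 24, which shrinks the detectable change by √24 = 4.9. A detectable change of 10% would therefore fall to about 2%, yet the sentence claims a tenfold reduction to 1%.

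This is the only statement in the article of how small a change the composition survey can detect. Programs to influence the nutrient content of processed foods, including reformulation, are among the candidate interventions, and this survey is what would show their effect on the food supply. A reader who relies on the printed power would put the chance of missing a true 1% change at 10%, when on the stated inputs it is about 59%. A non-significant result could then be taken as stronger evidence against a small market-wide change than the data can supply.

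**Working it through.** **Inputs.** All but alpha come from the section quoted above: n = 1200 products, taken as 1200 matched pairs (the best case); SD of the percentage change = 20; target power 0.9; effects of 1% (all products) and 10% (50 items). Alpha is not given there. I assume two-sided 5% and vary it below.

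**Formulas.** For a mean paired change:

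- SE = SD/√n
- power = Φ(δ/SE − z₁₋α/₂)
- detectable change at 0.9 power = (1.960 + 1.2816) × SE = 3.2415 × SE

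**The plan's 50-item figure.** SE = 20/√50 = 2.83. Power at 10% = Φ(10/2.83 − 1.96) = Φ(1.58) = 0.94 (noncentral t: 0.934). Detectable change = 3.2415 × 2.83 = 9.2%. This half holds, and it supports reading the calculation as a paired one with 20 as a standard deviation.

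**The plan's all-categories figure.** SE = 20/√1200 = 0.577. Power at 1% = Φ(1/0.577 − 1.96) = Φ(1.73 − 1.96) = 0.41 (noncentral t: 0.409). Detectable change = 3.2415 × 0.577 = 1.87%.

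**What the printed claim would need.** n = (3.2415 × 20/1)² ≈ 4,203 pairs (about 4,205 with the t distribution). With 1200 pairs, the SD would have to be √1200/3.2415 = 10.7.

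**Other readings of the 1% claim.**

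| Reading | Power at 1% |
|---|---|
| 1200 pairs, two-sided 5% | 0.41 |
| 1200 pairs, one-sided 5% (same as two-sided 10%) | 0.53 |
| 1200 pairs, one-sided 10% | 0.67 |
| 1200 v 1200 unpaired, two-sided 5% | 0.23 |
| Both countries pooled, 2400 pairs, two-sided 5% | 0.69 |
| Both countries pooled, 2400 pairs, one-sided 5% | 0.79 |
| Average of two follow-ups, correlation 0.5 to 0, two-sided 5% | 0.52 to 0.69 |
| 3 × 1200 counted as 3600 independent pairs, two-sided 5% | 0.85 |
| 3 × 1200 counted as 3600 independent pairs, one-sided 5% | 0.91 |

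Only the last row reaches 0.9. It treats three rounds of the same products as independent pairs, which is not the paired analysis described. Reading 20 as a variance gives power close to 1 at 1% and a detectable change of 0.42%, which does not match the printed figure either.

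**Incomplete matching (assumption, for illustration only).** If 60% of products were found at both rounds, 720 pairs would remain: SE = 20/√720 = 0.745, detectable change = 2.4%, power at 1% = Φ(1.34 − 1.96) = 0.27. The article gives no match rate.

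**The case against.** The strongest points on the other side concern weight and consequence, not the arithmetic.

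- **The calculation did not set the sample.** The shops surveyed are to cover more than 80% of the processed foods available, and 1200 is an expectation from the 2013 database. Correcting the sentence changes no procedure, and this outcome is one of several. That is true and is why the fix is cheap, but a stated power for a main outcome should still be right.
- **It may be a slip for 2%.** At 2% the same formula gives Φ(2/0.577 − 1.96) = 0.93, in line with the 50-item half. This is plausible, but the printed figure remains wrong.
- **Near-census coverage.** If about 80% of all products were covered (an assumption, since shop share is only a rough proxy), a finite-population correction would cut the SE to 0.577 × √0.2 = 0.26 and give power of about 0.97 at 1%. The article invokes no such correction, and its 50-item figure fits the uncorrected formula. The point is a caution against calling a 1% change undetectable under every framework; it does not support the sentence as written.
- **Unstated alpha, and unclear whether 1200 is per country.** Both are fair. The value 0.41 depends on two-sided 5%, but every version in the table that keeps to the described paired analysis stays below 0.9.
- **The analysis is estimation by mixed model.** Confidence intervals would show the true precision at the end. With two rounds and complete pairs, though, the model estimates the same mean paired change and adds no information. It can use products seen only once, so the 720-pair figure is a matched-pairs-only illustration and not a forecast.

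**Conclusion.** The concern holds. On the protocol's own inputs, and at two-sided 5%, power for a 1% change across all products is about 0.41 instead of 0.9, and the change detectable at 0.9 power is about 1.9%. With one-sided 5% these become 0.53 and 1.7%, so the conclusion does not rest on the assumed alpha. The SD is offered only as an example, but the sentence says the power holds even at that dispersion, and at that value it does not.

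The figure of 0.41 assumes that all 1200 products are matched and independent. Lost matches, or products that change together within a brand or category, would lower it. The 50-item figure is sound. The dietary-intake sample size is a separate calculation and is not touched by this point.

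**What to change.** Restate the sentence along these lines: with 1200 matched products and an SD of 20 for the percentage change, there is 0.9 power at a two-sided 5% level to detect a mean change of about 1.9% across all categories (power about 0.4 for 1%). Leave the statement for categories with 50 items unchanged. State the alpha, and say whether 1200 is per country.

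It would also help, though the correction does not depend on it, to give the detectable change for the number of products expected to be found at both rounds. For example, 720 pairs would give 2.4% if 60% matched; the team should supply its own match rate.

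The cost is one sentence and a less favourable stated sensitivity. No data collection, outcome or analysis has to change.

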#### Assessing food composition and price of processed foods

The objective of this survey is to measure and assess changes in salt and sugar levels in foods. For this, a standardised approach and a smartphone application will be used to collect data. FoodSwitch is a smart phone application originally developed in Australia and since launched in 7 other countries including the United Kingdom, China and India [57]. The FoodSwitch App can be used to collect food composition data based on back of pack Nutrient Information Panel, which is uploaded into a comprehensive database of nutrition composition. Salt and sugar levels and prices of processed foods in the market will be assessed in years 1 and 4 (2 and 5 for Samoa) at a similar time to the dietary surveys. Data will be collected from the shops that collectively provide the majority (more than 80%) of the processed foods available for purchase in Fiji and Samoa, using the same sampling strategy each year. Food products will be categorised using the existing FoodSwitch food categorisation system. The data fields collected for each product will be brand/manufacturer, product name, food category, serving size, sodium, total fat, saturated fat, and sugar per 100 g. The FoodSwitch App will be used to take photos of the front and back of the pack. Data are then extracted from pictures of the Nutrient Information Panel on the back of packs and inputted by data assistants. Brand/manufacturer name will be recorded in order to establish the proportion of packaged products that are imported compared to the proportion that are produced locally. Price data will be recorded separately. Lists of ingredients will also be recorded.

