### Systems thinking in community knowledge exchange (STICKE)

Building on the previous work done in Fiji [58], and informed by baseline outcome data and the policy landscape analysis, we will invite key government, industry and civil society leaders to participate in a structured, facilitated process [59] to build consensus on population level actions to reduce sugar and salt. We will engage 15–20 participants in each country, recruited through known contacts of the existing project team, in a series of deliberative consensus building forums. The objectives will be to understand diets and the drivers of poor diet, map existing interventions, and then discuss barriers and opportunities to strengthening policy implementation.

We will use techniques adapted from community based participatory system dynamics, notably group model-building and software (STICKE), to engage stakeholders in building a causal loop diagram reflecting the complexity of the drivers of unhealthy food availability and consumption and identify new or adapting existing interventions to reduce salt and sugar. Specific food policy interventions identified through a preliminary stakeholder meeting in January 2020 include:Taxes on foods or drinks high in salt or sugar – we will identify steps that need to be taken to strengthen existing implementation, including amending the level or type of taxation or extending to other foods.Programs to influence the nutrient content of available processed foods - we will identify new policies or opportunities to strengthen implementation of existing policies including engaging industry on reformulation or by working with importing agencies to change the balance of imports (i.e. having nutrient content restrictions to specify which foods that can be imported).School food policies and programs - we will review existing programs and identify opportunities to strengthen implementation and broaden reach including through training and capacity building and the strengthening of monitoring and accountability mechanisms.

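### The food-composition analysis names no manufacturer term and its power statement treats products as independent; if changes correlate within manufacturer, standard errors for the mean change will be too small

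*Protocol article*

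**What the plan says.** The section Data analysis and sample size of the protocol article sets the target of estimation: "We will estimate the paired change in salt and sugar levels between baseline data and each of the follow-up points". It then names the model: "We will analyse the change over time using linear mixed models which account for the repeated measurements". Repeated measurement is the only source of correlation mentioned.

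The power text in the same section starts from "it is expected that data on around 1200 products will be collected each year". It continues "Even if the percentage change in composition is highly dispersed (e.g. SD = 20", then "we should have 0.9 power to detect a 1% change in composition across all categories", "or a 10% change for food categories with 50 items". No design effect appears, and the significance level and sidedness are not given. The diet survey is treated differently: its sample-size section applies a design effect of 1.5.

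Two other sections bear on the point. Assessing food composition and price of processed foods lists brand/manufacturer among the data fields and gives one reason for it: "Brand/manufacturer name will be recorded in order to establish the proportion of packaged products that are imported". The STICKE section describes one intervention option as including "engaging industry on reformulation or by working with importing agencies to change the balance of imports". Salt and sugar levels in foods are among the main outcome measures listed in Methods.

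**The concern.** Recipes are decided by companies, and one decision can cover several products. If industry engagement works, products of one manufacturer are likely to change together. A product-level random effect represents the link between measurements of the same product in different rounds. It does not represent the tendency of different products from one company to move together, and that tendency sets the uncertainty of the mean paired change.

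With a positive correlation of this kind, an analysis with products as the only units has standard errors that are too small and confidence intervals that are too narrow. It also reports reformulation too often when there is no general change. The power statement makes the same independence assumption.

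**Working it through.** **Inputs from the article:** 1200 products per round, SD of percentage change 20, power 0.9, a 1% change across all categories, a 10% change with 50 items.

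**Inputs assumed:** significance level 0.05, two-sided unless noted; every product paired; equal numbers of products per manufacturer, *m*; within-manufacturer correlation of change, ICC. The article gives neither *m* nor ICC, so a range is shown.

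**Step 1: the article's own figures, with independent products.** Power = Φ(δ / (SD/√n) − 1.96).

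- All categories: SD/√n = 20/√1200 = 0.577, and 1/0.577 = 1.732. Power = Φ(1.732 − 1.96) = 0.41 (0.53 one-sided). The stated 0.9 is not reproduced.
- Detectable change at 0.9 power: (1.960 + 1.282) × 0.577 = 1.87%. A 1% change would need about 4203 pairs, or an SD of about 10.7 with 1200 pairs.
- Category of 50: 20/√50 = 2.828, and 10/2.828 = 3.536. Power = Φ(3.536 − 1.96) = 0.94. The detectable change is 9.2%, so this statement is met with a small margin.

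**Step 2: add manufacturer clustering.** Design effect DE = 1 + (m − 1) × ICC. The true SE is √DE times the SE under independence. If clustering is ignored, type I error = 2 × (1 − Φ(1.96/√DE)). The detectable change becomes 1.87% × √DE.

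| Products per manufacturer | ICC | DE | SE multiplier | Type I error if ignored | Detectable change at 0.9 power |
|---|---|---|---|---|---|
| independent | 0 | 1.0 | 1.00 | 5% | 1.87% |
| 3 | 0.05 | 1.10 | 1.05 | 6.2% | 1.96% |
| 6 | 0.10 | 1.50 | 1.22 | 11.0% | 2.29% |
| 6 | 0.20 | 2.00 | 1.41 | 16.6% | 2.65% |
| 6 | 0.30 | 2.50 | 1.58 | 21.5% | 2.96% |
| 12 | 0.10 | 2.10 | 1.45 | 17.6% | 2.71% |
| 24 | 0.30 | 7.90 | 2.81 | 48.6% | 5.26% |

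**Step 3: the category statement.** Power for a 10% change stays at or above 0.9 only while DE does not exceed (10/9.17)² = 1.19. Five products per manufacturer with ICC 0.05 gives DE 1.20 and power just under 0.90. With ICC 0.10, DE is 1.40 and power 0.85. Ten products with ICC 0.30 gives DE 3.7 and power 0.45.

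**The case against.** - **The sentence does not exclude manufacturer.** A reader might infer that the model handles repeated measurements and nothing else. The article does not say so. It is a condensed account, and the full random-effects structure may be in an analysis plan that is not shown. Likewise, one stated reason for recording brand/manufacturer does not rule out other uses. This stands against any claim that the term has been ruled out. It does not cover the published power statement, which contains no allowance for clustering.
- **Harm is not certain.** A reader might also infer that the standard errors are bound to be materially wrong. No figure in the article fixes cluster size or ICC, and with 3 products per manufacturer and ICC 0.05 the SE error is about 5%. This stands; the conclusion has to be conditional.
- **The target of inference matters.** The shops sampled supply more than 80% of the processed foods on sale. If the target is the change in that market alone, one large company reformulating its range is a real reduction and not a false positive. This narrows the point. However, the power calculation treats product changes as random draws with an SD, and on that view their dependence has to be counted.
- **The mechanism is partial.** Taxes, school policies and a changed balance of imports are also options, and the last works largely through products entering or leaving the market. That is fair, but such products have no pair. The paired change mainly reflects recipe change in products that stay on sale.
- **The remedy has limits.** Brand may not identify the company that decides the recipe. At 6 products per manufacturer, a 50-item category has only about 8 clusters (50/6), too few for uncorrected cluster-robust standard errors. Both limits stand and shape the fix.

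**Conclusion.** The point holds in conditional form. As described, the analysis names only repeated measurements, and the power statement assumes independent products, while company-level reformulation is a planned route of change on a main outcome. If changes correlate positively within manufacturer, a product-only model understates the standard error of the mean paired change.

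The size cannot be fixed from the article. Across the assumed settings, the type I error runs from barely above nominal to several times nominal. The 10% category statement has almost no room for clustering.

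The 1.87% used as the starting point is the figure for 1200 independent pairs, not the article's 1%. The shortfall for the 1% claim is a separate fault that does not depend on clustering, and clustering would only lower that power further.

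**What to change.** 1. **Model.** Say that the change model has manufacturer as a level above product (brand where the manufacturer cannot be identified), with a random intercept and a random time effect. The time effect is essential: an intercept alone cancels from a paired change and would leave its standard error essentially unchanged. For the all-category analysis, manufacturer cluster-robust standard errors are an alternative. For categories with few manufacturers, use the random-effects version or a small-sample correction.
2. **Power text.** State that the figures assume independent products. Restate the all-category claim so that it follows from its inputs: about 1.87% at 0.9 power with 1200 pairs and SD 20, two-sided. Preferably, also show the effect of a design effect, with the assumed products per manufacturer and ICC given.

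The cost is low. Brand/manufacturer is already collected, so the change needs a model term and a few sentences, plus some work to link brands to manufacturers. The downside is somewhat wider confidence intervals.

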#### Assessing implementation and compliance with school food policies

Both Fiji and Samoa undertake regular surveys of the school food environment and compliance with healthy school food policies. In Samoa, data is collected on food availability and the food environment within each school at least annually and reported through a multisectoral coordination mechanism [30]. In Fiji, the Ministry of Education, Cultural Heritage and Arts is responsible for implementation and monitoring the Policy on School and Food Canteen. Despite these measures, compliance to healthy food policies has not improved significantly over time. We will analyse these data to generate a baseline report of compliance to standards for Samoa and Fiji. We will also review the policies to understand the degree to which they are likely to be reducing the promotion and availability of foods high in salt and sugar

### Systems thinking in community knowledge exchange (STICKE)

Building on the previous work done in Fiji [58], and informed by baseline outcome data and the policy landscape analysis, we will invite key government, industry and civil society leaders to participate in a structured, facilitated process [59] to build consensus on population level actions to reduce sugar and salt. We will engage 15–20 participants in each country, recruited through known contacts of the existing project team, in a series of deliberative consensus building forums. The objectives will be to understand diets and the drivers of poor diet, map existing interventions, and then discuss barriers and opportunities to strengthening policy implementation.

We will use techniques adapted from community based participatory system dynamics, notably group model-building and software (STICKE), to engage stakeholders in building a causal loop diagram reflecting the complexity of the drivers of unhealthy food availability and consumption and identify new or adapting existing interventions to reduce salt and sugar. Specific food policy interventions identified through a preliminary stakeholder meeting in January 2020 include:Taxes on foods or drinks high in salt or sugar – we will identify steps that need to be taken to strengthen existing implementation, including amending the level or type of taxation or extending to other foods.Programs to influence the nutrient content of available processed foods - we will identify new policies or opportunities to strengthen implementation of existing policies including engaging industry on reformulation or by working with importing agencies to change the balance of imports (i.e. having nutrient content restrictions to specify which foods that can be imported).School food policies and programs - we will review existing programs and identify opportunities to strengthen implementation and broaden reach including through training and capacity building and the strengthening of monitoring and accountability mechanisms.

On completion of the policy landscape analysis, government, industry and civil society leaders will convene every 6 months. The logic model represented by the causal loop diagram built using STICKE will be used to; (i) inform selection of interventions and discuss additional survey data required for monitoring, (ii) use quantitative and qualitative evidence to strengthen intervention implementation, (iii) review interim impact, based on regular monitoring data, and (iv) review the process of implementation to inform feasibility of scale-up, including through recommendations to strengthen monitoring.

A provisional logic model outlining the intended outputs and outcomes of the interventions is provided in Fig. 2.

